##### Concomitant therapy

All concomitant medications taken during the study will be documented with the indication, dose information and dates of administration.

#### Provisions for post-trial care {30}

At the end of the intervention, unless policies change, participants will revert to the standard of care treatment. The study budget is not in a position to fund post-study care or implementation of weekly DP as policy. However, the investigators will be working in close collaboration with local (Ministry of Health) and international policymakers (e.g. WHO) to ensure that policymakers are informed early of any pertinent research findings.

### Outcomes {12}

#### Primary efficacy outcome

The primary efficacy outcome is the incidence of clinical malaria defined as a history of fever in the preceding 48 h or documented axillary temperature of ≥ 37.5 °C, plus *P. falciparum* parasites on microscopic examination of a blood smear by a certified malaria microscopist.

#### Key secondary outcomes

Clinic visits because of blood smears or malaria rapid diagnostic tests (RDT) confirmed non-severe and severe malariaAll-cause sick-child clinic visits after enrolmentIncidence of malaria parasitaemiaAll-cause hospital admissions after enrolmentAll-cause and malaria-specific hospitalisationSCA-related vaso-occlusive events (including severe pain events and dactylitis), acute chest syndrome, stroke and need for blood transfusionAll-cause mortality after enrolment

#### Other outcomes

##### Safety outcomes

Incidence of serious adverse events (SAEs; grade 3 or 4 adverse events) according to the Common Terminology Criteria for Adverse Events (CTCAE) toxicity tables and coded using MedDRAAdverse events (grade 1 or 2 toxicity) after enrolmentIncidence of serious cardiac adverse events (convulsions or syncope within 48 h after drug intake)Change in QTc length and QTc-prolongation on four-monthly ECG recordings and by the age-dependent cut-off value (in a subset of patients)

##### Tolerance

Vomiting the study drug within 30 min of administration of the study medicationIncidence of gastrointestinal complaints after enrolment

##### Operational feasibility, acceptability, uptake and compliance

User and provider experiences of the interventionUser satisfaction with the interventionUser treatment preferenceAdherence

##### Cost-effectiveness

Provider costs of delivering the interventions and provider costs of managing malaria in SCA childrenDirect and indirect costs of patients receiving the interventions and managing cases of malariaIncremental cost-effectiveness of replacing current standards of care (SP) with DP from the perspectives of the health care provider and the societyHealth-related quality of life

##### Genetic markers of resistance

Development of markers of resistance to piperaquine such as plasmepsins 2 and 3Range of antimicrobial resistance in bacterial isolates on blood and urine culture in febrile children

### Participant timeline {13}

Participant timeline is presented in Fig. 1.

**Fig. 1 Fig1:**
[figure not shown]
Showing study flow chart

### Sample size {14}

The minimum incidence rate of clinical malaria in SCA patients receiving monthly SP is estimated at 0.2 events per year. Assuming an effect size of 50% if DP is used (i.e. a 50% reduction in the rate as in Bigira et al. [27] that is, a hypothesised incidence rate of 0.1 events per person per year in the DP group), at a power of 0.9 and 0.05 level of significance, we will need 438 individuals to be followed up for 18 months. Allowing for 20% losses to follow-up, we shall need 548 participants (274 in each group) to be followed for an average of 18 months, equivalent to 9864 person months, or 824 participants for an average follow-up of 12 months, equivalent to 9888 person-months.

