## Data collection and management

### Plans for assessment and collection of outcomes {18a}

Before study onset, all the assessors (clinical, nursing, laboratory, pharmacy and data) will undergo study-specific training on study procedures. The internal and external monitors will independently document readiness in the site initiation visits before recruiting the first participant. Twice annual refresher training will be carried out and especially following the subsequent interim monitoring visits.

Following the enrolment visit, participants will return for follow-up at 2 months and then every 2 months thereafter until the required person-months of observation is achieved. The study will refund the costs of transport to the clinic and provide a time compensation. At each visit, all clinical events in the intervening period will be ascertained and those previously not reported or for which the patients did not attend the study clinic will be documented. Participants with < 80% adherence at any one point will have additional counselling.

To determine the outcomes, any participant with a history of fever in the previous 48 h or temperature ≥ 37.5 °C on any visit will have a blood smear for malaria microscopy performed by a certified malaria microscopist. All other SCA-related and non-SCA-related events such as painful crises and hospitalisations will also be documented and reported. In this way, the point prevalence at each visit and the incidence of malaria can be estimated for each study arm without contaminating the intervention in either arm.

The study will provide a standard of care clinical services for sick visits and refer for appropriate care if the level of care required is beyond the capacity of the clinic. All these episodes will be reported as adverse events according to severity. All the adverse events (AEs) and serious adverse events (SAEs) during the intervening period will be documented following ICH GCP principles and all SAEs reported to regulatory bodies, sponsors, DSMB and ethics committees.

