### Interim analyses {21b}

Only one interim efficacy analysis is planned to assess the primary outcome when the study reaches approximately 50% follow-up time, i.e. about 412 person-years follow-up per study arm time accumulated across all study sites or at least half of the estimated number of events (62 out of an anticipated 124 events across both arms). This information will be used to determine if the study should continue as planned, proceed with modifications or be terminated. The Haybittle–Peto boundary will be used as a stopping rule, which states that a trial could be stopped early if an interim analysis shows a probability ≤ 0.001 that a difference as extreme or more between the treatments is found, given that the null hypothesis is true.

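### The person-month totals (9864 or 9888) and the 124 anticipated events deduct nothing for the planned 20% loss, so stated power, duration, events and interim trigger cannot all agree

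*Protocol article*

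**What the plan says.** Protocol article, Sample size {14}: "The minimum incidence rate of clinical malaria in SCA patients receiving monthly SP is estimated at 0.2 events per year", with "a hypothesised incidence rate of 0.1 events per person per year in the DP group". Then "at a power of 0.9 and 0.05 level of significance", "we will need 438 individuals to be followed up for 18 months". The next sentence begins "Allowing for 20% losses to follow-up" and goes on: "we shall need 548 participants (274 in each group) to be followed for an average of 18 months, equivalent to 9864 person months". An alternative of 824 participants at an average of 12 months is given as 9888 person-months.

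Plans for assessment and collection of outcomes {18a}: children return at 2 months and "every 2 months thereafter until the required person-months of observation is achieved". No number is given there. The only person-month totals in the article are 9864 and 9888.

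Interim analyses {21b}: one efficacy look at roughly half the follow-up time, put at about 412 person-years in each arm, or at half or more of the expected events, "62 out of an anticipated 124 events across both arms". The boundary is Haybittle–Peto at 0.001.

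Assessment of efficacy (under Statistical methods {20a}): children who die, withdraw or are lost are censored at that date or at their last visit, so their time before that counts. Negative-binomial regression replaces Poisson if there is overdispersion.

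**The concern.** The 20% allowance exists so that, after losses, about 438 children's worth of follow-up is actually observed. Multiplying the inflated 548 by a full 18 months removes the loss that the inflation was meant to cover. The same is true of 824 × 12 and of the event total built on it.

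This has practical effect because follow-up is said to run to a required person-month total, and the single efficacy look is timed against an event count and a person-time figure. The protocol does not say whether 9864/9888 is time to be observed or time nominally enrolled. Under either meaning at least one figure that the trial relies on is wrong: the power, the achievable duration, the event total or the interim fraction.

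**Working it through.** **Inputs.** Rates of 0.2 and 0.1 per person-year, power 0.9, alpha 0.05, 18 months, 20% loss (all from Sample size {14}); 1:1 allocation (Trial design {8}). Sidedness is not stated; two-sided reproduces the plan's number and one-sided gives 358.

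**1. Reproduce the plan's sample size** (Wald test on the log rate ratio).
- Person-years per arm = (1.960 + 1.2816)² × (1/0.2 + 1/0.1) / (ln 2)² = 328.05.
- 328.05 / 1.5 = 218.7, so 219 per arm and 438 in all, as stated.
- 438 / 0.8 = 547.5, so 548, as stated.

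**2. Reproduce the person-months and events.**
- 548 × 18 = 9864 person-months = 822 person-years; 824 × 12 = 9888 = 824 person-years.
- The average rate over two equal arms is 0.15. 824 × 0.15 = 123.6, the stated 124 (822 × 0.15 = 123.3).
- Both totals match only with no loss deducted.

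**3. Person-time that matches 90% power.**
- 438 × 18 = 7884 person-months = 657 person-years, or 328.5 per arm.
- Expected events: 657 × 0.15 = 98.6; half is about 49.

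**4. Consequences under each meaning of the target.** Power = Φ(ln 2 / √(15 / person-years per arm) − 1.960).

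| Person-time actually observed | Person-years per arm | Expected events | 62 as a share | Power |
|---|---|---|---|---|
| 7884 (lost children contribute nothing) | 328.5 | 98.6 | 63% | 90.0% |
| 8878 (lost children contribute half: an assumption; 548 × 0.9 × 18) | 369.9 | 111.0 | 56% | 93.1% |
| 9864 | 411 | 123.3 | 50% | 95.2% |
| 9888 | 412 | 123.6 | 50% | 95.3% |

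**5. Can 548 children with 20% loss reach 9864 observed?**
- Lost children contribute nothing: 9864 / 438 = 22.5 months per retained child.
- Lost children contribute half: 9864 / (548 × 0.9) = 20.0 months.
- For 824 children and 9888: 9888 / (824 × 0.8) = 15.0 months, or 9888 / (824 × 0.9) = 13.3 months, against the stated 12.

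**6. The interim person-time trigger.**
- 412 per arm × 2 = 824 person-years, which is 100% of the target and corresponds to about 124 events.
- Half the target is 412 over both arms, 206 per arm, and 412 × 0.15 = 61.8 events. The two alternative triggers therefore differ by a factor of two.

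**The case against.** A reader might infer two things at once: that 62 events is not half the information, and that the stopping target does not match the stated power. The documents do not support both together, because they need opposite meanings of the target. If 9864 person-months are observed, about 124 events are expected and 62 is half. If 9864 is only enrolled time, 62 exceeds half, but the trial then has its stated 90% power or a little more. A reader might also infer that the trial is underpowered; no row of the table shows that.

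Other points on the plan's side:
- That 9864/9888 is the end-of-follow-up target is an inference, since the outcome-assessment section gives no number. This stands. It is also the reason clarification is needed, because no other total is available to use.
- The 63% and 22.5 months assume that lost children contribute no time, whereas the analysis section censors them at their last visit. This stands, so those values are the extremes of a range.
- The 18 months is an average, and the abstract allows 548 to 824 children, so a person-time target could be met by enrolling more. This stands in part: 685 children with 20% contributing nothing would give 685 × 0.8 × 18 = 9864. It does not rescue the specific pairing of 548 with 18 months or 824 with 12 months after a 20% loss.
- The interim trigger asks for half or more of the events, and the boundary is 0.001. This stands: a look at 56–63% has little effect on type I error.
- Cutting the target to 7884 would remove a margin. This stands. The 438 assumes pure Poisson counts. With negative-binomial dispersion of 0.5 to 1 (an assumption), 219 per arm over 1.5 years gives about 87–84% power, and 274 per arm about 93–91%.

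**Conclusion.** The inconsistency is real: the stated person-months and event total are built on the loss-inflated enrolment at full follow-up, and the 90% power belongs to 7884 person-months, a total the article never states. Its effect depends on a choice that the protocol leaves open.

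- Target observed: power is about 95% where 90% is stated, the 62-event trigger is correct, and the stated durations fall short (about 20 to 22.5 months are needed with 548 children).
- Target enrolled: about 99 to 111 events are expected in place of 124, the 62-event look falls at about 56–63%, and power is about 90–93%.

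The error leads to excess follow-up or a somewhat later look. It costs no power and introduces no bias. The figures rest on the plan's own rates, a two-sided test, Poisson counts, and lost children contributing between none and half of their planned time. The person-time trigger of 412 person-years per arm is wrong against the plan's own total whichever meaning is chosen. The numbers should be restated, but the validity of the trial is not threatened.

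**What to change.** State whether the required person-months are observed or enrolled, and make the sample size, follow-up and interim sections agree. There are two coherent versions:

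- **Smaller target:** 7884 observed person-months (657 person-years), about 99 events, 90% power, interim at about 329 person-years over both arms or about 49–50 events.
- **Larger target:** keep 9864/9888 observed and about 124 events, state power of about 95%, and set the interim at about 412 person-years over both arms (about 206 per arm) or 62 events. Remove the implication that 548 children with 20% loss reach it in 18 months, or 824 in 12, and give the duration or enrolment that does.

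The larger target is the safer choice, because the calculation has no allowance for the overdispersion that the analysis section anticipates. In either version, replace the figure of 412 person-years per arm.

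The smaller target costs only restated text and gives up the margin. The larger one also requires accepting longer follow-up or an enrolment above 548 within the range already given. Either restatement should be made without sight of unblinded results.

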### Recruitment {15}

Recruitment will be done simultaneously across all sites and will be competitive between the sites in the trial.

## Assignment of interventions: allocation

### Sequence generation {16a}

An independent statistician will generate the randomisation sequence in randomly varying block sizes stratified by site and weight band and keep the randomisation code in a locked computer file.

### Concealment mechanism {16b}

Allocation concealment is achieved by having patients randomised to DP also receive an SP placebo, and those on SP will, in addition, receive a DP placebo.

### Implementation {16c}

The randomisation list and the dummy codes generated by the independent statistician and the allocation sequence will be forwarded to the trial pharmacists in Uganda and Malawi to prepare sequentially numbered, sealed envelopes for the participants. The pharmacists will prepare the subject-specific study drugs by site and weight bands following the randomisation scheme. Participants will be enrolled competitively, assigned a registration number in sequential order, and treatment arm by trial staff.

## Assignment of interventions: blinding

### Who will be blinded {17a}

All study staff will be blinded to the treatment assignment, including the investigators, outcome assessors and trial statisticians. In addition, both the participants and caregivers will also remain blind to the intervention arms assigned to individual patients. The randomisation code will be kept in a locked computer file with the independent statistician and made available to the chair of the DSMB on request.

### Procedure for unblinding if needed {17b}

Emergency unblinding will be on an individual basis to ensure that the blinding of other participants is not affected. It will be considered if a suspected unexpected serious adverse reaction to the study drug (SUSAR), serious adverse reaction to the study drug or serious expected adverse drug-drug interactions between the study drug and other drugs provided to the participant undergoing treatment, as judged by the study physician or study safety monitor. The first alert will be raised by the study physician within 24 h of becoming aware of the event in an expedited report to the chief investigator, ethics committees, safety monitor, sponsor and DSMB chair. The final decision will be advised by the country’s principal investigator and/or the chief investigator in consultation with the safety monitor and/or DSMB chair. If clinically indicated, the subject will be withdrawn from receiving further study drugs. Other than the written or verbal disclosure of the code in any of the confidential correspondence about the participant between the principal or chief investigator and the safety monitor or the DMSB chair, the actual allocation will NOT be disclosed to the participant and/or other study personnel including other site personnel, monitors, corporate sponsors or project office staff.

Unblinding of data in nested studies such as the pharmacokinetic study will be done by independent statisticians not involved in the main trial to ensure the blinding of other participants is not affected. A database with the results of the nested study and the corresponding data from the main trial for these participants will be emailed to the trial statistician. The trial statistician will pseudonymise the data, such that the personal data can no longer be attributed to a specific study subject without the use of additional information.

## Data collection and management

### Plans for assessment and collection of outcomes {18a}

Before study onset, all the assessors (clinical, nursing, laboratory, pharmacy and data) will undergo study-specific training on study procedures. The internal and external monitors will independently document readiness in the site initiation visits before recruiting the first participant. Twice annual refresher training will be carried out and especially following the subsequent interim monitoring visits.

Following the enrolment visit, participants will return for follow-up at 2 months and then every 2 months thereafter until the required person-months of observation is achieved. The study will refund the costs of transport to the clinic and provide a time compensation. At each visit, all clinical events in the intervening period will be ascertained and those previously not reported or for which the patients did not attend the study clinic will be documented. Participants with < 80% adherence at any one point will have additional counselling.

To determine the outcomes, any participant with a history of fever in the previous 48 h or temperature ≥ 37.5 °C on any visit will have a blood smear for malaria microscopy performed by a certified malaria microscopist. All other SCA-related and non-SCA-related events such as painful crises and hospitalisations will also be documented and reported. In this way, the point prevalence at each visit and the incidence of malaria can be estimated for each study arm without contaminating the intervention in either arm.

The study will provide a standard of care clinical services for sick visits and refer for appropriate care if the level of care required is beyond the capacity of the clinic. All these episodes will be reported as adverse events according to severity. All the adverse events (AEs) and serious adverse events (SAEs) during the intervening period will be documented following ICH GCP principles and all SAEs reported to regulatory bodies, sponsors, DSMB and ethics committees.

### Plans to promote participant retention and complete follow-up {18b}

To minimise losses to follow-up and be able to follow-up participants, contact mobile cell phone numbers will be recorded at recruitment and a sketch map of the home location of the study participant drawn. A study home visitor will document the route home together with Global Positioning Satellite (GPS) data of the home. In the event the participant does not attend the scheduled follow-up visits, this information will be used for tracing.

### Data management {19}

#### Data collection

Data will be collected and recorded at the point of contact by one of the trained study staff. The study will use a combination of paper-based (baseline and study end) and electronic record forms. Barring logistical difficulties, all intervening nursing and clinical data will be entered directly into password-protected databases. We will use the Research Electronic Data Capture (REDCap™), a secure, web-based international data capture system. This will be hosted at servers at Global Health Uganda and the Training and Research Unit of Excellence in Malawi.

#### Data sharing

At the end of the study, anonymised data will be available to other researchers for further analysis, subject to ethical approval, the terms of the original patient consent and agreement on its use according to prevailing laws on intellectual property rights.

#### Archiving

Hard copies of CRFs will be stored long-term at secure storage facilities for a minimum of 5 years. Data will also be kept electronically in a public data repository in compliance with prevailing laws on data storage.

#### Data quality and standards

The quality of the electronic and questionnaire data collection and data entry will be maximised through the training of field staff in standardised questionnaire administration, in the methodology for collecting data and all staff will be expected to demonstrate competence before conducting fieldwork. All electronic CRFs and data validation processes for data will incorporate range and consistency checks.

#### Managing, storing and curating data

Verified and validated data will be stored via the cloud on a secure server. The investigators will have access to the site data on the central server. Locally, data will be backed-up continuously on a secure off-site server and/or encrypted standalone hard drives. Once the data validation phase is completed by the central data manager, the database will be locked and transferred to a statistical programmer who will do further syntax-driven consistency checks and syntax-driven data cleaning (e.g. in Stata). Once data entry and cleaning are complete, hard copies of CRFs will be stored long-term at secure storage facilities in Malawi and Uganda as per local storage policies and guidelines. Data will also be kept electronically in compliance with prevailing laws on data storage. The research data will be stored for the long term in the original electronic format, in a large unified database and a public database that contains all research data other than participant identifiable data.

### Confidentiality {27}

All information regarding the participants will remain confidential to the extent allowed by law. Unique numerical identifiers will be used for data entry. All screening forms and case report forms will be kept in a secured location with access limited to authorised study staff. Unique numerical identifiers will be used for the computer-based data entry and blood samples. Publications will contain only aggregated data. No identifying information will be included to ensure individual patient anonymisation of all data and results made public.

